### Outcome measures

Primary outcome

Primary outcome measure will be the change in haemoglobin concentration determined by blood test at baseline, first and second follow-up and end-line survey in the interventional compared with the control arm. Other variables that will be assessed along with the main primary outcome include maternal weight gain, gestational age and blood pressure.

ii. Secondary outcomes

Secondary outcome measures will include the change in nutritional knowledge and dietary practices determined by standard questionnaire at baseline, first and second follow-up and end-line surveys in the interventional compared with the control arm. Other variables that will be assessed along with secondary outcome include still birth, Appearance, Pulse, Grimace, Activity, and Respiration (APGAR) score, birth weight and new-born mortality.

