### Sample size calculation and selection

The sample size will be calculated based on the formula for a randomized control study [29].
$$n=\frac{{\left\{Z\alpha \sqrt{\left[\pi o\left(1-\pi o\right)\right]}+Z\beta \sqrt{\left[\pi 1\left(1-\pi 1\right)\right]}\right\}}^{2}}{{\left(\pi 1-\pi o\right)}^{2}}$$
where *n* is the minimum sample size, *Zα* is the standard normal deviate (1.96) at 95% confidence level for this study, *Zβ* is the standard normal deviate (0.84) with a power of demonstrating a statistically significant difference before and after the experiment between the two groups at 90%. *πo* is the proportion at pre-intervention (baseline prevalence of anaemia 50%). *π*1 is the proportion after intervention (prevalence of anaemia after intervention proportion 35%).
$$178=\frac{{\left\{1.96\sqrt{\left[0.5\left(1-0.5\right)\right]}+0.84\sqrt{\left[0.35\left(1-0.35\right)\right]}\right\}}^{2}}{{\left(0.35-0.5\right)}^{2}}$$

With the adjustment for 10% attrition, the calculated sample size will be *n* = 198 (178/0.9). Therefore, a total of 200 pregnant women from each arm (interventional and control) will be recruited for the study. The study arms will be matched in the ratio of 1:1. A list of all wards will be obtained from the administrative authority of Dodoma City. From the list, wards from peri-urban areas will be listed and assigned random numbers. Simple random sampling technique will be used to select four peri-urban wards. Two wards based on geographical area will be assigned to the interventional arm and the remaining two wards to the control arm. From each ward, community health workers and local leaders will recruit eligible participants and invite them at a recommended and agreed place to conduct the study.

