### Data processing and analysis

Data will be cleaned, edited and coded before data analysis. Statistical Package for Social Sciences version 25.0 will be used to analyse the data. Descriptive statistics will be used to generate frequency distribution, mean, standard deviation and cross tabulation to describe the characteristics of the study participants. The comparisons between interventional and control arms will be determined using independent *t*-tests and comparisons within groups (pre/post) will be estimated using paired *t*-tests. The *P* <0.05 will be considered statistically significant. Regression analysis will be conducted to determine the predictors of haemoglobin concentration.

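### Between-arm t-tests on change leave the baseline value unadjusted for knowledge, dietary practices and haemoglobin; adjusting for it, inside an analysis that accounts for ward, would usually be more precise.

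*Protocol article*

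**What the plan says.** Under Outcome measures, Secondary outcomes, the article states: "Secondary outcome measures will include the change in nutritional knowledge and dietary practices determined by standard questionnaire". Measurement is to be at four surveys, with the arms set against each other: "determined by standard questionnaire at baseline, first and second follow-up and end-line surveys in the interventional compared with the control arm". The primary outcome in the same section is also a change, in haemoglobin, over the same four surveys.

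Under Data processing and analysis: "The comparisons between interventional and control arms will be determined using independent *t*-tests". Paired t-tests are reserved for within-arm comparisons. The only regression named has another purpose: "Regression analysis will be conducted to determine the predictors of haemoglobin concentration". It is not described as the comparison of arms, and it does not cover knowledge or diet. The Abstract draws the same link, naming changes after baseline as the main outcomes and independent t-tests as the between-group method.

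Under Randomization, two eastern and two western wards are selected, and one side of the city goes to each arm.

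**The concern.** The second and third objectives (knowledge, and dietary intakes and practices) rest on a test that subtracts the whole baseline value from each woman's later value. That is fully efficient only when the two values are almost perfectly correlated. At lower correlations the subtraction adds noise, and below a correlation of 0.5 the change score is noisier than the follow-up value alone. Since the baseline is already collected in both arms, the plan may give up precision that would cost nothing to keep.

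The second issue is the starting level. With two wards per arm, all from one side of the city, the arms may well differ at baseline. The change contrast and the baseline-adjusted contrast then estimate the effect under different assumptions about what happens to that difference, and the plan fixes one of them without comment.

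**Working it through.** **The plan's own figures.** No sample size or power is given for knowledge, diet or mean haemoglobin change, so there is nothing to reproduce for these outcomes. The stated 178 per arm concerns anaemia prevalence. The printed formula with its printed inputs gives (1.96×0.5 + 0.84×√0.2275)²/0.15² = 84.7, so 178 is not reproduced. That is a separate matter and does not enter below.

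**Inputs.**
- From Sample size calculation and selection: 200 women per arm and 10% attrition, so about 180 per arm.
- From Randomization: two wards per arm, so about 90 women per ward.
- Assumed, because the document gives no value: baseline-to-follow-up correlation r of 0.3, 0.5 and 0.7; equal variances at both times; a range of ward intracluster correlations (ICC).

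**Step 1. Precision, ignoring wards.** In units of the outcome variance, the per-woman variance is 2(1−r) for a change score, 1 for the follow-up value alone, and 1−r² with baseline adjustment. The ratio of change to adjusted is 2(1−r)/(1−r²) = 2/(1+r).

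| r | Change | Adjusted | Ratio | SE reduction with adjustment |
|---|---|---|---|---|
| 0.3 | 1.40 | 0.91 | 1.54 | 19% |
| 0.5 | 1.00 | 0.75 | 1.33 | 13% |
| 0.7 | 0.60 | 0.51 | 1.18 | 8% |

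Equivalently, 180 women per arm analysed on change match 180(1+r)/2 = 117, 135 or 153 per arm with adjustment. The difference detectable with 80% power, (1.96+0.84)×√(2v/180) with v the per-woman variance, is 0.35, 0.30 and 0.23 SD on change, against 0.28, 0.26 and 0.21 SD adjusted.

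**Step 2. Unequal starting levels.** Per 1 SD of baseline gap, if the gap regresses with slope r, the change contrast shifts by −(1−r): −0.7, −0.5 and −0.3 SD. If the gap persists in full, the change contrast does not shift, and individual-level adjustment leaves (1−r) of the gap uncorrected. For example, a 0.25 SD gap at r = 0.4 gives 0.25×0.6 = 0.15 SD, charged to the change score in the first case and to the adjusted model in the second.

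The SD of a chance baseline gap is √(2[1+89×ICC]/180): 0.15, 0.18, 0.25 and 0.33 SD at ICC 0.01, 0.02, 0.05 and 0.10, against √(2/180) = 0.105 SD under individual randomisation. Gaps of this order are plausible.

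**Step 3. Precision with persistent ward differences.** Suppose each ward's deviation is the same at both times. It cancels from the change score, so the variance of the arm contrast stays (2/180)×2(1−r). An individual-level adjusted model with slope r keeps (1−r) of the deviation, and its variance is (2/180)(1−r²) + (1−r)²×ICC×(89/90). Setting the two equal, (1−r)² cancels and the break-even is ICC = 1/89 = 0.011, whatever r is. At r = 0.5:
- ICC 0.01: change 0.0111, adjusted 0.0108. Adjustment is slightly better.
- ICC 0.02: change 0.0111, adjusted 0.0133. Change is better.

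If ward differences do not persist, this penalty on adjustment does not arise in that form.

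**The case against.** A t-test on change is a legitimate method. Under random allocation it is unbiased over repeated randomisations, and baseline adjustment is an efficiency refinement. That stands and limits the weight of the point. The method is nevertheless written into the article, so it is not merely a detail left to an analysis plan.

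Three stronger readings are tempting, and the documents do not support them.

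- *A baseline difference between East and West distorts the change contrast.* This holds only if the difference regresses to the mean. A side of the city that starts and stays higher is corrected in full by the change score and only in part by individual-level adjustment. A score ceiling cannot be invoked either: the article describes questionnaire sections on knowledge and diet but gives no score, range or maximum. That the arms will start unequal is likely, not stated.
- *The trial gives up a known amount of power.* With an assumed 0.3 SD effect one can compute 67% against 85% at r = 0.3, and 81% against 91% at r = 0.5. The effect size and r are not in the document, and the figures ignore wards. They show relative loss only.
- *Adding a baseline covariate is enough.* A model with only arm and baseline would still treat about 360 women as independent, although wards are randomised.

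Nor is the point confined to the secondary outcomes, since haemoglobin change is compared in the same way. Finally, if the t-test were meant for follow-up values rather than change, the shift would be +r per SD of baseline gap, so the baseline would still matter.

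**Conclusion.** The point holds as a minor, conditional improvement. The plan compares arms on change without baseline adjustment for knowledge, diet and haemoglobin. At the individual level, with equal variances, this costs precision for every r below 1: the variance is 1.54, 1.33 and 1.18 times the adjusted one at assumed r of 0.3, 0.5 and 0.7, and the loss becomes small as r approaches 1. Those ratios leave out ward clustering. With about 90 women per ward and fully persistent ward differences, the advantage vanishes near an ICC of 0.011 and reverses above it.

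No direction or size of bias can be asserted. The change contrast moves by (1−r) times any baseline gap that regresses, while a gap that persists favours the change score, and the document does not settle which applies. The ward clustering ignored by the t-test, and the alignment of arm with side of city, are larger problems that this point leaves untouched.

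**What to change.** In Data processing and analysis, replace the independent t-test as the main between-arm analysis. For each follow-up knowledge and dietary-practice measure, and for haemoglobin, fit a model containing arm and the woman's baseline value of the same measure: linear for quantitative measures, logistic for yes/no items. Place it within an analysis that accounts for ward. Report the unadjusted change comparison as a sensitivity analysis, so that readers can see whether the conclusion depends on how a baseline gap is treated. Fix this choice before outcome data are seen, because the two contrasts can differ when the arms start unequal.

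The cost is revised wording and slightly more analysis work; no new data or visits are needed. The downside is possible under-correction of a persistent East–West difference, which is why the change analysis should be kept. The amendment does not remedy having two wards per arm or the confounding of arm with side of city.

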### Sample size calculation and selection

The sample size will be calculated based on the formula for a randomized control study [29].
$$n=\frac{{\left\{Z\alpha \sqrt{\left[\pi o\left(1-\pi o\right)\right]}+Z\beta \sqrt{\left[\pi 1\left(1-\pi 1\right)\right]}\right\}}^{2}}{{\left(\pi 1-\pi o\right)}^{2}}$$
where *n* is the minimum sample size, *Zα* is the standard normal deviate (1.96) at 95% confidence level for this study, *Zβ* is the standard normal deviate (0.84) with a power of demonstrating a statistically significant difference before and after the experiment between the two groups at 90%. *πo* is the proportion at pre-intervention (baseline prevalence of anaemia 50%). *π*1 is the proportion after intervention (prevalence of anaemia after intervention proportion 35%).
$$178=\frac{{\left\{1.96\sqrt{\left[0.5\left(1-0.5\right)\right]}+0.84\sqrt{\left[0.35\left(1-0.35\right)\right]}\right\}}^{2}}{{\left(0.35-0.5\right)}^{2}}$$

With the adjustment for 10% attrition, the calculated sample size will be *n* = 198 (178/0.9). Therefore, a total of 200 pregnant women from each arm (interventional and control) will be recruited for the study. The study arms will be matched in the ratio of 1:1. A list of all wards will be obtained from the administrative authority of Dodoma City. From the list, wards from peri-urban areas will be listed and assigned random numbers. Simple random sampling technique will be used to select four peri-urban wards. Two wards based on geographical area will be assigned to the interventional arm and the remaining two wards to the control arm. From each ward, community health workers and local leaders will recruit eligible participants and invite them at a recommended and agreed place to conduct the study.

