### Study design and population

The study design will be a community-based cluster randomized controlled trial with both control and interventional arms. Four hundred pregnant women at second trimester of pregnancy (gestational age from 13 weeks and above) living in peri-urban areas of Dodoma City at the time of data collection and willing to participate will be included in the study. Pregnant women with special medical conditions, such as epilepsy, sickle cell anaemia, diabetes mellitus, hypo- or hyperthyroidism, malignancy disease, hypertension, human immunodeficiency virus, ante-partum haemorrhage, renal disease and severe anaemia will be excluded from the study. ANC card and health worker will assist in identifying the eligible participants.

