### Randomization

The unit of randomization will consist of wards. Wards from peri-urban areas will be grouped into two groups based on geographical area (Eastern and Western wards). A total of four wards will be randomly selected as follows: two wards from the East and remaining two wards from the West part of the city. The two groups of wards will be randomly assigned to the study arms as follows: one group to the interventional arm and another group to the control arm, respectively. This will be carried out to ensure that interventional wards are bundled together but far away from control wards in order to minimize contamination. A statistician who will not be the part of this study will do the final randomization of wards to the interventional and control arms.

The flow chart of the study design is shown in Fig. 1.

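### The sample size for this ward-randomised trial has no design effect and uses the 80% deviate, so the stated 90% power is not delivered

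*Protocol article*

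**What the plan says.** Under Study design and population: "The study design will be a community-based cluster randomized controlled trial with both control and interventional arms". Under Randomization: "The unit of randomization will consist of wards". That section also places the wards in an Eastern and a Western group and gives one whole group to each arm, so that intervention and control wards lie far apart and contamination is limited.

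Under Sample size calculation and selection: "The sample size will be calculated based on the formula for a randomized control study". The calculation is printed in full. Its inputs are:

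- Zα, which "is the standard normal deviate (1.96) at 95% confidence level for this study"
- Zβ, which "is the standard normal deviate (0.84) with a power of demonstrating a statistically significant difference", with the power put at 90% ("before and after the experiment between the two groups at 90"%)
- a reference proportion of 0.50 ("baseline prevalence of anaemia 50"%) and a proportion after intervention of 0.35.

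The result is given as 178 per arm, divided by 0.9 for attrition to give 198, and rounded to 200. The same section fixes the number of clusters: "Simple random sampling technique will be used to select four peri-urban wards", two for each arm.

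Data processing and analysis names independent t-tests for the comparison between arms. Outcome measures names change in haemoglobin concentration as primary.

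**The concern.** Women in one ward share diet, season, malaria exposure and clinic services, so their outcomes are likely to be correlated. With about 100 women per ward, even a small correlation removes much of the information that 200 women per arm appear to carry. The calculation has no term for this. It is worked from inputs to final n, so the omission is not a detail that a condensed article leaves to a fuller document. The numbers of wards and women are also design decisions that a later analysis plan cannot repair.

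There is a risk in each direction. If the analysis respects the wards, a null result would come from a trial far weaker than its stated power. If the analysis treats women as independent, a positive result could be spurious. The Discussion looks ahead to national scale-up, so either error would carry weight.

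**Working it through.** **1. The plan's own figure.** Put the printed values into the printed formula:

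{1.96·√(0.5·0.5) + 0.84·√(0.35·0.65)}² / 0.15² = (0.980 + 0.401)² / 0.0225 = 1.906 / 0.0225 = **84.7**, not 178.

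Doubling gives 169.4. With Zβ = 1.28, the deviate for 90% power, the printed formula gives 112.4. Standard two-sided two-proportion formulas give, per arm:

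- 80% power: 167 (unpooled), 170 (pooled), 183 (continuity-corrected)
- 90% power: 223, 227 and 240 respectively.

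None gives 178 exactly. It lies among the 80% values and well below the 90% values. The attrition step, 178/0.9 = 198, is correct.

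**2. Power with no clustering.** With 10% attrition, 200 per arm leaves 180.

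- Variance sum: 0.25 + 0.2275 = 0.4775.
- SE = √(0.4775/180) = 0.0515.
- 0.15/0.0515 = 2.912.
- Power = Φ(2.912 − 1.96) = **83%**.

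So 90% is missed at ICC 0. This part of the gap comes from Z = 0.84 and not from clustering.

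**3. Adding clustering.** The article gives no ICC, so the values below are assumptions. Equal wards are also assumed, with m = 90 analysed per ward.

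- Design effect: DE = 1 + 89·ICC.
- Effective n per arm: 180/DE.
- SE = √(0.4775·DE/180).
- Normal power: Φ(0.15/SE − 1.96).
- Ward-level power: noncentral t with 4 − 2 = 2 df, critical value 4.303.

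| ICC | DE | Effective n per arm | Power, normal | Power, 2 df |
|---|---|---|---|---|
| 0 | 1.00 | 180 | 83% | 37% |
| 0.005 | 1.45 | 125 | 68% | 29% |
| 0.01 | 1.89 | 95 | 56% | 24% |
| 0.02 | 2.78 | 65 | 42% | 18% |
| 0.05 | 5.45 | 33 | 24% | 12% |

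If 80% was the intended power, it needs 0.15/SE ≥ 2.80. That means DE ≤ (2.912/2.80)² = 1.082, or ICC ≤ 0.082/89, about 0.001.

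**4. More women in the same four wards.** As m grows, SE cannot fall below √(0.4775·ICC/2).

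- ICC 0.02: the limit is 0.0691, which caps power at 58% (normal) or 24% (2 df).
- ICC 0.005: the 2-df cap is about 62% (limit 0.0346; 0.15/0.0346 = 4.34).
- Even by the normal approximation, 90% needs 0.15/SE ≥ 3.24, so it is out of reach at any ward size once the ICC exceeds 2·(0.15/3.24)²/0.4775, about 0.009.

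**5. False positives if women are analysed as independent.** Rate = 2·{1 − Φ(1.96/√DE)}.

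- ICC 0.01: 1.96/√1.89 = 1.426, about **15%**.
- ICC 0.02: 1.96/√2.78 = 1.176, about **24%**.

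**6. The same women over more wards.** Take 14 of the 15 peri-urban wards, with 360/14 = 25.7 analysed in each and 12 df. DE is 1.25 at ICC 0.01 and 1.49 at ICC 0.02. Power is about **67%** and **59%**.

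**The case against.** The strongest objections concern cause, consequence and remedy. The omission itself is plain in the printed calculation.

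- *A reader might infer that clustering alone explains the gap to 90%.* The article does not support that. Power is already about 83% at ICC 0, because 90% is paired with the 80% deviate. The loss from clustering should be counted from 83%.
- *The 2-df figures do not describe the planned test.* This stands. Data processing and analysis names independent t-tests and no ward-level analysis. The 2-df series is 37% even at ICC 0, so much of that drop comes from having four wards and not from the missing design effect. It shows what a ward-level test could deliver.
- *A reader might infer that the only danger is an uninformative null result.* Under the tests as named, run on individuals, the danger is an inflated false-positive rate. Which risk applies depends on the analysis used.
- *A reader might infer that spreading the 400 women over more wards repairs the design at little cost.* It does not. The Randomization section allocates whole East and West groups. If that stays, 14 wards still form two allocated blocks and 12 df is not justified. If wards are randomised singly, intervention and control wards may adjoin, which the section sets out to avoid. Power would still be below 80%.
- *The sizing outcome is not the primary outcome.* This also stands. The article gives no target difference or standard deviation for haemoglobin change, so power for that outcome cannot be derived. Haemoglobin is still measured within wards, so the change of outcome does not remove the clustering.

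**Conclusion.** The point holds. The stated 90% power is wrong as written for two separable reasons: the deviate used is that for 80%, and the formula ignores randomisation by ward. The first leaves about 83% and needs no assumed ICC. The second lowers this to between about 68% and 24% by the normal approximation for ICCs of 0.005 to 0.05, or to between 29% and 12% for a ward-level test on 2 df. The printed equation does not yield 178 either.

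The size of the clustering loss rests on assumed ICCs, equal wards and 10% attrition, and applies to anaemia prevalence only. The 2-df figures also treat the four wards as separately allocated. With whole geographical groups allocated, they are if anything generous. It is not shown that the trial lacks power for haemoglobin change, only that the article does not establish it.

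**What to change.** In Sample size calculation and selection:

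1. Remove the 90% claim, make the Z value agree with whatever power is stated, and correct the equation so that it gives the number reported.
2. State an assumed ICC range with its source, the design effect 1 + (m − 1)·ICC, and the resulting power for four wards with small-sample degrees of freedom.
3. Say that, over the ICC range in the table, adding women in the same four wards cannot restore 90% power, or even 80%, for a ward-level test.
4. Say that this power refers to prevalence. If inputs for haemoglobin change are available, give the matching calculation.
5. State that the between-arm comparison will account for wards, so that the restated power and the test agree.

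These are changes of wording and calculation and cost little.

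Before recruitment, the sponsor may also consider spreading the same 400 women over more of the 15 peri-urban wards. That means randomising single wards in place of whole East and West groups, with added travel and ward permissions and a greater risk of contamination. At 14 wards, power would be about 67% (ICC 0.01) or 59% (ICC 0.02), and the text should say so if this route is taken.

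### The sample-size equation gives 85, not 178, and its Zβ of 0.84 corresponds to 80% power, so the stated 90% power is wrong

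*Protocol article*

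**What the plan says.** All of the statements are in the protocol article, and all but the significance threshold are under Sample size calculation and selection.

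- Zα is the "standard normal deviate (1.96) at 95% confidence level for this study". The threshold agrees with Data processing and analysis, where P "<0.05 will be considered statistically significant".
- For Zβ and the power, the article writes: "standard normal deviate (0.84) with a power of demonstrating a statistically significant difference before and after the experiment between the two groups at 90" (per cent).
- The proportions are "baseline prevalence of anaemia 50" per cent (π₀) and "prevalence of anaemia after intervention proportion 35" per cent (π₁).
- The symbolic formula is n = {Zα√[π₀(1−π₀)] + Zβ√[π₁(1−π₁)]}² / (π₁−π₀)². The article repeats it with 1.96, 0.84, 0.5 and 0.35 put in and equates it to 178.
- The 178 is divided by 0.9 for 10% attrition to give 198. The result is applied per arm: "a total of 200 pregnant women from each arm (interventional and control) will be recruited for the study". On allocation, "The study arms will be matched in the ratio of 1:1".

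**The concern.** The paragraph contradicts itself in two places that can be checked from its own figures. A Zβ of 0.84 is the familiar value for 80% power, but the text says 90%. The substituted equation also does not look as if it could reach 178. Behind the second point is a formula of the wrong type: each term holds the variance of a single proportion, which is the form for comparing one sample with a fixed value, while the trial compares two arms.

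This paragraph is the article's only justification for enrolling 400 women. If its power statement is wrong, a non-significant result may be given more weight as evidence of no effect than the design supports.

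**Working it through.** **Inputs** (all from the article): Zα = 1.96, Zβ = 0.84, π₀ = 0.50, π₁ = 0.35, allocation 1:1, attrition 10%, 200 recruited per arm. The variances are 0.50 × 0.50 = 0.25 and 0.35 × 0.65 = 0.2275. The squared difference is 0.15² = 0.0225.

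**1. The plan's own equation.**
{1.96 × 0.5 + 0.84 × 0.47697}² / 0.0225 = {0.98 + 0.40065}² / 0.0225 = 1.9062 / 0.0225 = **84.7, so 85**. The article prints 178. Two simple repairs also fail:
- doubling the printed expression gives 169.4;
- using the 90% deviate of 1.2816 gives 112.5.

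**2. The power label.** Φ(0.84) = 0.7995, which is 80% power. For 90%, Zβ = 1.2816.

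**3. A two-arm comparison of 50% with 35%, two-sided 5%, independent women.**
- Unpooled: n = (Zα + Zβ)² × (0.25 + 0.2275) / 0.0225. At 80% power this is 2.80² × 0.4775 / 0.0225 = 166.4, so 167. At 90% it is 223.0, so 223.
- Pooled, with mean proportion 0.425: n = {Zα√(2 × 0.425 × 0.575) + Zβ√0.4775}² / 0.0225. At 80% this is {1.3703 + 0.5805}² / 0.0225 = 169.1, so 170. At 90% it is {1.3703 + 0.8856}² / 0.0225 = 226.2, so 227.
- Pooled with continuity correction: 183 at 80% and 240 at 90%.

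None of these gives 178 exactly.

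**4. Power at the planned sizes** (pooled form): power = Φ{(0.15√n − 1.3703) / 0.6910}.

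| Analysed per arm | Power |
|---|---|
| 178 | 81.9% |
| 180 (200 less 10%) | 82.4% |
| 200 (no losses) | 86.1% |

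None reaches 90%. At 178 the false-negative risk is 100 − 81.9 = about 18%.

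**5. Size for a true 90%.** 227 analysed per arm, and 227 / 0.9 = 252.2, so 253 recruited per arm.

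**6. The attrition step.** 178 / 0.9 = 197.8, so 198. This step is correct.

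**The case against.** **The number 178 is not arbitrary.** It lies between the plain two-arm size at 80% power (167 to 170) and the continuity-corrected size (183). An unpooled continuity-corrected calculation gives 179.5. The 200 recruited per arm also exceeds 170 / 0.9 = 189. All of this stands. The result of 85 therefore shows that the printed equation is wrong, not that the trial is twice as large as it needs to be: two-arm power at 85 per arm is only about 51%. The same comparison also shows that the planned size is an 80% size, which supports the finding on power.

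**Other readings might rescue 90%.** A one-sided 5% test at 90% power needs 182 (unpooled) to 185 (pooled), close to 178, but it contradicts both printed deviates. A literal one-sample reading at 178 gives about 98% power, which is not 90% either, and the trial compares two arms. Neither reading helps.

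**It could be a text-extraction fault or an error in the cited source.** The symbolic and substituted formulas have the same structure, and the substituted values match the prose, so extraction is an unlikely cause. The article cites a source for the formula. Whether that source or the transcription is at fault cannot be told, and it does not change the result.

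**The 82% is not this trial's real power either.** This is fair. It treats women as independent, while four wards are randomised, two per arm. It also concerns anaemia prevalence, while the primary outcome is change in haemoglobin concentration. The article gives no intracluster correlation. If one assumes 0.01 to 0.05 with 90 analysed women per ward, the design effect is 1.89 to 5.45 and nominal power falls to about 55% to 23%, before allowing for so few wards. Clustering is the larger power problem, but it is a separate one. It only moves power further from 90%, so the present error stands without it.

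**Conclusion.** The concern holds. Two contradictions are certain from the article alone: 0.84 is the deviate for 80% power and not 90%, and the printed equation equals 84.7 and not 178. The formula printed is also not one for comparing two arms.

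For 50% against 35% at two-sided 5%, with independent women, the plan delivers about 82% power at 178 to 180 analysed per arm and at most 86% if all 200 are analysed. The stated 90% would need about 223 to 227 analysed per arm. At the individual level the defect lies in the formula and the power claim; the planned size is adequate for 80%. These powers are upper bounds for this design, because they make no allowance for ward clustering.

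**What to change.** Rewrite the sample-size paragraph:

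- Replace the printed formula with the two-proportion formula, naming the version used, and print a substituted line that computes.
- Remove the 90% claim, so that the stated power agrees with Zβ = 0.84.
- State what the planned size gives for 50% against 35% at two-sided 5%: about 82% power at 178 analysed per arm. Label it as before any allowance for clustering, and do not present it as the trial's final power until the clustered figure stands beside it.

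The cost is the wording of one paragraph and a less favourable power statement. No extra women are needed. If the sponsor did intend 90%, the label could be kept only by raising the size to about 227 analysed, or 253 recruited, per arm. That is 53 more per arm and 106 in total, still with no clustering allowance.
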